##### Economic evaluation parameters

3.9.3.4

###### Target subjects

3.9.3.4.1

Patients who participated in the clinical trial at least once starting with V2 will be included in the economic evaluation.

###### Economic evaluation parameters and criteria

3.9.3.4.2

The medical costs generated as a result of this clinical trial will be calculated through a medical cost analysis in the economic evaluation. If necessary, the health insurance and medical costs at the present institution may be used to represent a portion of the unit costs. A sensitivity analysis will be performed on the medical costs.

1.Primary economic outcomes(a)Cost per QALY gained(b)The EQ-5D will be used to estimate the quality of life needed to calculate the QALY. Quality of life will be used as the primary economic outcome. The area-under-the-curve method will be used to calculate the QALYs.2.Secondary economic outcome(a)Effectiveness indices such as the cost per NRS3.Economic evaluation period

The initial analysis will take 4 weeks. If further estimation is necessary after 4 weeks, the costs and effectiveness will be extrapolated using a regression model, or secondary analyses such as a decision analysis will be performed.

Medical costs generated as a result of this clinical trial will be calculated based on the number of treatment sessions and unit costs. Researchers will determine and record the medical costs generated inside the clinical trial institution by reviewing the electronic records after they are unblinded.

If the time horizon exceeds 12 months, the unit of cost will be unified to the South Korean won of 2017, and a 5% discount will be applied in accordance with the economic evaluation guideline by the Health Insurance Review and Assessment Service. The analytical point of view of this study is society's point of view. The representative values (e.g., mean, etc) of the parameters used in this study will be used in a baseline analysis. A probabilistic sensitivity analysis will be performed using the distributions of all the estimated parameters and their representative values.

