## Introduction

1

Total knee replacement (TKR) is a surgical procedure that is being increasingly performed due to population aging and increased life expectancy in South Korea. The number of TKR procedures increased by over 135%, from 45,879 in 2015 to 62,344 in 2019. The medical cost of public health insurance associated with TKRs totaled 37,077,059,000 won (∼32,638,256 US dollars) in 2015 and increased to 55,499,427,000 won (∼48,850,829 US dollars) in 2019.^[1]^ The age distribution of patients undergoing TKR shows that 36.2% of the patients were aged 60 to 69 years, 48.6% were aged 70 to 79 years, and 8.7% were aged ≥80 years,^[2]^ indicating that TKR is primarily performed on elderly patients. A large number of patients undergo TKR due to degenerative knee arthritis. Consistent with the high incidence of TKR in South Korea, the number of patients seeking acupuncture for pain management and enhancement for rehabilitative therapy effects and bodily function not only before but also after TKR has also been increasing.

In the western-medicine-based clinical settings in South Korea, acupuncture treatment after TKR is considered unsafe regardless of the acupuncture points in use because of the risk of infection and reoperation, and the practice is often rejected or prohibited. Furthermore, according to a recent systematic review, including acupuncture in a rehabilitation program is beneficial as an adjunct to opioids for pain management across several types of postsurgical conditions.^[3]^ However, the results of studies investigating the effect of acupuncture after TKR are not in concordance.^[4–7]^ Moreover, no previous study has examined the efficacy, safety, and cost-effectiveness of post-TKR acupuncture rather than focusing solely on its efficacy.

Therefore, it is worth assessing the effectiveness, safety, and cost-effectiveness of acupuncture as an adjunctive therapy in patients following TKR in a pilot study.

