## Objective

2

The aim of this study is to verify the hypothesis that the concurrent use of acupuncture treatment and usual care after TKR is more effective, safe, and cost-effective relieving TKR symptoms than usual care therapy alone.

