#### General principle for statistical analysis

3.9.1

An intention-to-treat (ITT) analysis will be performed as the primary analysis for patients who receive acupuncture at least once. A per-protocol analysis will also be performed for participants who have completed the study after excluding dropouts.

For intergroup comparisons, an independent *t* test will be performed for continuous variables if normality is satisfied. If normality is not satisfied, the Wilcoxon rank-sum test, a nonparametric statistical technique, will be performed. For comparisons between different time points within each group, a paired *t* test or Wilcoxon signed rank test will be used. An analysis of covariance (ANCOVA) adjusted for covariant factors that show significant differences with respect to the baseline in each treatment group and the initial baseline outcomes will be additionally determined. For categorical variables, the chi-square test or Fisher's exact test will be used.

All statistical analyses will be two-tailed with a 5% significance level. The last observation carried forward (LOCF) method will be used to handle missing values. Multiple imputation or a regression analysis will be additionally used to examine differences in the results.

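### The plan promises to verify cost-effectiveness through a cost-per-QALY ratio in 25 patients per arm; mean differences and net monetary benefit, framed as estimation, would serve better

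*Protocol article*

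**What the plan says.** The Abstract and the Objective set out to verify a hypothesis that acupuncture plus usual care is "more effective, safe, and cost-effective relieving TKR symptoms than usual care therapy alone". The Introduction speaks of assessing the "cost-effectiveness of acupuncture as an adjunctive therapy in patients following TKR in a pilot study".

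Section 3.9.3.4.2 names the primary economic outcome as "Primary economic outcomes(a)Cost per QALY gained". On the QALY it says "The area-under-the-curve method will be used to calculate the QALYs", with utilities from EQ-5D. The same item also states "Quality of life will be used as the primary economic outcome". The initial economic analysis covers 4 weeks, with extrapolation or decision modelling if more is needed. On uncertainty it says "A probabilistic sensitivity analysis will be performed using the distributions of all the estimated parameters and their representative values", and it adds a sensitivity analysis on costs.

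Section 3.2 places EQ-5D at baseline, 2 weeks and 4 weeks. Section 3.3 derives 22 per group, raised to 25 for dropout, from an assumed K-WOMAC difference. No economic quantity enters that calculation.

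**The concern.** Cost-effectiveness is one of three parts of the stated hypothesis, and the plan words it as something to be verified. The chosen summary is a ratio whose denominator, the QALY difference, may be close to zero in a sample this small. Two problems follow.

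- **Interval.** When the CI of the denominator includes zero, the ratio has no ordinary bounded confidence interval.
- **Sign.** A negative ratio arises both when acupuncture looks cheaper and better and when it looks dearer and worse. The number alone does not separate these opposite conclusions.

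A single cost-per-QALY figure from this trial could then be quoted as support for either position. In addition, the sentence naming quality of life as primary does not match a primary outcome that contains cost.

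**Working it through.** **1. The plan's own figure.** Pooled SD = √[(4.05² + 4.16²)/2] = 4.105, and d = 3.60/4.105 = 0.877. For a two-sided 5% t test, exact noncentral t power is 79.2% with 21 per group and 81.1% with 22. So 22 reproduces, and 22/0.9 = 24.4 gives 25. The sample supports a standardised difference of about 0.88 on K-WOMAC; the document says nothing about what it supports for QALYs.

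**2. Inputs for the QALY difference.** From the documents: 25 per arm; EQ-5D at 0, 2 and 4 weeks; area under the curve. Assumed, because the documents give no values: utility SD 0.10 to 0.20; correlation ρ between visits 0.3 to 0.7; equal baselines; the same utility gain g at weeks 2 and 4.

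**3. Formulas.** The trapezoid weights are (1, 2, 1)/52.
- QALY difference = 3g/52. For g = 0.05 this is 0.0029; for g = 0.10 it is 0.0058.
- Unadjusted SE = (SD/52) × √(6 + 10ρ) × √(2/25). The term 6 + 10ρ is 9, 11 or 13 at ρ = 0.3, 0.5 or 0.7.
- SE adjusted for baseline utility: replace 6 + 10ρ by 6 + 10ρ − (1 + 3ρ)², which is 5.39, 4.75 or 3.39.
- The SE therefore runs from 0.0016 to 0.0039 unadjusted and from 0.0010 to 0.0025 adjusted.

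**4. Share of trials whose 95% CI for the QALY difference includes zero** (normal approximation, over the whole grid of SD and ρ):

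| Gain g | Unadjusted | Baseline-adjusted |
|---|---|---|
| 0.05 | 58% to 89% | 18% to 79% |
| 0.10 | 6% to 69% | 0% to 37% |

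Unadjusted, the estimated QALY difference is zero or negative in 4% to 23% of trials at g = 0.05 and in 0% to 7% at g = 0.10.

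**5. Role of the horizon.** Difference/SE = 3g / [SD × √(6 + 10ρ) × √(2/25)]. The factor 1/52 cancels, and so would any common spacing between the visits. With a constant gain, a longer horizon enlarges the difference and its SE alike. The imprecision comes from n.

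**6. What the ratio can look like.** Further assumptions, for illustration only: extra cost 200,000 won with SD 500,000, independent of the QALY; g = 0.05, SD 0.15, ρ = 0.5, unadjusted.
- The true ratio is 200,000/0.00288, about 69 million won per QALY.
- SE of the cost difference = 500,000 × √(2/25) = 141,421 won; SE of the QALY difference = 0.0027.
- In simulation, the central 95% of observed ratios runs from about −650 to +770 million won per QALY.
- About 13% of trials show acupuncture as dearer and worse and about 7% as cheaper and better. Both groups report a negative ratio.

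**The case against.** The strongest reply is that every percentage rests on utility inputs that the documents do not contain, and that the range is wide. This stands. A reader might infer that the trial will probably produce a meaningless ratio and decide nothing; the documents do not support that. At a gain of 0.10 with baseline adjustment, the QALY difference is separated from zero in at least 63% of trials across the whole grid. Section 3.9.1 does foresee a supplementary ANCOVA that adjusts for baseline outcomes, although it does not name QALYs. The planned probabilistic sensitivity analysis can express decision uncertainty even when the denominator's interval includes zero, and a longer horizon is allowed.

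Other tempting readings also go too far:
- **The 4-week horizon as the cause.** Step 5 shows otherwise under a constant gain. The short horizon makes the QALY difference small and leaves out later effects, which is a separate matter.
- **No willingness-to-pay threshold.** A condensed article may leave this to the full protocol or analysis plan.
- **Cost and QALY drawn separately in the sensitivity analysis.** The text does not say so.
- **Costs moved to a rank test.** Section 3.9.1 says "If normality is not satisfied, the Wilcoxon rank-sum test, a nonparametric statistical technique, will be performed", but the economic section has its own methods and states no test on costs.
- **Medians in place of means.** The loose wording about representative values does not show that these would be used.

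It can also be said that quality of life is mentioned only as the ingredient of the QALY. That is the likely intent, but the sentence as printed names a different primary outcome.

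The reply does not remove two stated choices: a ratio as the primary economic outcome, and a promise to verify cost-effectiveness in a sample sized for another endpoint.

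**Conclusion.** The point holds in a limited form. The verification wording is stronger than 25 per arm can be shown to support, and a ratio is a poor primary summary when its denominator may not be distinguishable from zero. Under the assumed SD and correlation ranges, that happens in 58% to 89% of trials unadjusted and 18% to 79% adjusted at a utility gain of 0.05. At a gain of 0.10 it happens in 6% to 69% and 0% to 37%. These ranges are conditional on assumed EQ-5D inputs and equal baselines, so they show a material risk and not a forecast.

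The K-WOMAC analysis is unaffected. The change is worth making because a better analysis is available from data the trial already plans to collect.

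**What to change.** - In the Abstract and the Objective, word the economic aim as estimating cost-effectiveness, in line with the Introduction's description of a pilot.
- In section 3.9.3.4.2, make the primary economic analysis the difference in arithmetic mean cost, the difference in mean QALY adjusted for baseline EQ-5D, and the incremental net monetary benefit over a stated range of willingness-to-pay values.
- Take the 95% CIs and an acceptability curve from a bootstrap that resamples patients within arm and keeps each patient's cost and QALY together.
- Keep cost per QALY as a descriptive figure, reported with its quadrant on the cost-effectiveness plane.
- Reconcile the sentence naming quality of life as the primary economic outcome with cost per QALY.

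The cost is revised wording, a short bootstrap program and a little more analysis work, with no new data. The price is a more modest economic claim.

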###### Handling the data from dropouts

3.9.3.4.3

For drop-outs, the last obtained measurements will be used for all the remaining visits to make it seem as if the measurements were obtained during those visits (LOCF: last-observation-carried-forward analysis).

###### Exceptions to the exclusion criteria for the economic evaluation

3.9.3.4.4

Participants who drop out or are excluded due to the treatment effects or adverse effects of acupuncture or due to the worsening of the disease will be subject to an economic evaluation as long as the evaluation is feasible. The economic evaluation will be continued for the following dropout cases due to treatment effects or adverse effects.Cases: Drop-out due to recovery or loss of symptoms during the treatment period, drop-out due to the adverse effects from a drug, and treatment-related drop-out deemed by our researchers as associated with the target disease or the treatment provided in this clinical trial due to the secondary occurrence of a disease (e.g., surgical site infections, etc).These exceptional cases will be included in the ITT analysis as there is a high possibility that the effect estimates will go missing during the study. The LOCF will again be used to estimate the missing values. However, in cases in which the missing pattern is not monotone, multiple imputation can be used to check the sensitivity.

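### The economic evaluation has two conflicting rules for drop-outs: everyone seen from V2, or only those whose reason for leaving is on a list

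*Protocol article*

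**What the plan says.** All references are to the protocol article.

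- **Section 3.9.3.4.1 (Target subjects):** "Patients who participated in the clinical trial at least once starting with V2 will be included in the economic evaluation". It sets no condition on completing the trial or on the reason for leaving.
- **Section 3.9.3.4.3 (Handling the data from dropouts):** "For drop-outs, the last obtained measurements will be used for all the remaining visits". Again there is no condition on reason or arm.
- **Section 3.9.3.4.4 (Exceptions to the exclusion criteria for the economic evaluation):** the lead sentence keeps, where feasible, "Participants who drop out or are excluded due to the treatment effects or adverse effects of acupuncture or due to the worsening of the disease". Next comes "The economic evaluation will be continued for the following dropout cases due to treatment effects or adverse effects", with three cases. The first two are "Drop-out due to recovery or loss of symptoms during the treatment period, drop-out due to the adverse effects from a drug". The third is "treatment-related drop-out deemed by our researchers as associated with the target disease or the treatment provided in this clinical trial", with surgical site infection as an example of the secondary illness meant. It then says "These exceptional cases will be included in the ITT analysis", with LOCF again for missing values and multiple imputation as a possible sensitivity check.

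Three other places bear on this. Section 3.8.4 lists the reasons for early termination. Section 3.6 says that neither investigator nor participant can be blinded to the intervention, although evaluation is meant to be blinded. Section 3.2 and Table 1 place randomisation at V1, before surgery and before V2.

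**The concern.** Exceptions to exclusion make sense only if drop-outs are otherwise excluded. Sections 3.9.3.4.1 and 3.9.3.4.3 exclude none of them. Two analysts working from this text could therefore build different economic data sets, and the primary economic outcome, cost per QALY, would depend on which section they followed.

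If section 3.9.3.4.4 governs, whether a patient is kept or followed depends on why that patient left. That reason arises after randomisation and can be related to treatment and to outcome. Participants know their arm, the staff judging the third case may know it, and adverse effects of acupuncture can lead to retention only in the acupuncture arm. The groups compared on cost and QALYs are then no longer guaranteed to be the groups that were randomised.

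**Working it through.** **1. Which drop-outs does each rule keep?** Take the reasons in section 3.8.4 for a patient already seen at V2. Sections 3.9.3.4.1 and 3.9.3.4.3 keep the patient in every case. Section 3.9.3.4.4 gives:

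- Eligibility violation, withdrawal of consent, compliance below 70%, protocol violation: not listed.
- Adverse reactions: listed if due to acupuncture or a drug; otherwise only through the third, judged case.
- Other reasons accepted by the researchers: depends on the reason. Recovery would qualify; dissatisfaction with the allocated arm would not.

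The rules agree only for the listed reasons.

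**2. Can the sections be reconciled?** There are two ways to read section 3.9.3.4.4.

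- *As a rule on inclusion.* Unlisted drop-outs are out of the analysis. This contradicts section 3.9.3.4.1.
- *As a rule on follow-up only.* Everyone from V2 stays in, but evaluation continues only for listed reasons. The set is then consistent, but post-drop-out EQ-5D and costs are observed for some leavers and carried forward for others, according to reason. The sentence on inclusion in the ITT analysis would also have no function.

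Both readings leave a dependence on the reason for leaving. The ITT label does not settle the matter, because section 3.9.1 ties ITT to having had at least one acupuncture session, which no usual-care patient meets as worded.

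**3. How many patients?** Inputs from section 3.3: difference 3.60, SDs 4.05 and 4.16, two-sided alpha 0.05, power 80%, drop-out 10%.

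- The two-sample t-test calculation gives 20.9 per group (SD 4.05) to 21.96 (SD 4.16), so the stated 22 is reproduced. Then 22 / (1 − 0.10) = 24.4, rounded up to 25, as stated.
- Expected drop-outs: 25 × 0.10 = 2.5 per arm, 5 in total.
- Let f be the share of an arm's drop-outs whose reason qualifies. On the inclusion reading, patients kept = 25 − 2.5 × (1 − f). The protocol gives no f, so the values below are assumptions.

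| f, acupuncture | f, usual care | Kept, acupuncture | Kept, usual care |
|---|---|---|---|
| 1 | 1 | 25 | 25 |
| 0 | 0 | 22.5 | 22.5 |
| 0.5 | 0.5 | 23.75 | 23.75 |
| 0.6 | 0.3 | 24.0 | 23.25 |
| 0.8 | 0.2 | 24.5 | 23.0 |

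Section 3.9.3.4.1 keeps 25 v 25 if nobody is lost before V2. Section 3.9.3.4.4 keeps 22.5 to 25 per arm. Equal counts do not guarantee comparable groups: the patients kept could have left because of recovery in one arm and worsening in the other.

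**The case against.** The strongest objection is that the text selects by reason and never by arm. Several stronger readings are tempting, and the document does not support them.

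- **That drop-outs are treated differently by arm.** No section says so. Worsening disease, recovery, adverse effects of a drug and surgical site infection can occur in either arm, since both have surgery and the same critical-pathway drugs. Only adverse effects of acupuncture are confined to one arm. An imbalance is possible, not prescribed, and with equal f the counts match.
- **That favourable exits are kept only under acupuncture.** "Drop-out due to recovery or loss of symptoms during the treatment period" is not tied to acupuncture, so a usual-care patient who recovers is kept on the same words. An acupuncture patient who leaves from dislike of needling also fits no listed case.
- **That the whole list is at the researchers' discretion.** Their judgement attaches to the third case only, and section 3.9.3.4.4 does not say which researchers judge or whether they know the arm.
- **That recovery clashes with section 3.8.4.** It is not named there, but the item for other accepted reasons can cover it.
- **That a QALY bias can be calculated.** Suppose three usual-care drop-outs were frozen at utility 0.50 from week 2 while the true value rose to 0.70 by week 4. The arm mean would fall by 0.5 × 0.20 × (2/52) × (3/25) = 0.00046 QALY, about 12% of 0.05 × (4/52) = 0.00385. That shows LOCF applied to one arm only, with assumed utilities. The protocol names LOCF for listed and other drop-outs alike, so similar freezing in both arms would largely cancel. It does not measure this defect.

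Costs within the institution come from electronic records (section 3.9.3.4.2), a source that does not need a drop-out's questionnaire. That narrows the exposure, mainly to EQ-5D and outside costs.

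These points remove the arm-specific claims. They leave the conflict between the sections and the selection by reason. Nor is this detail left to an analysis plan: the article states both rules, and they disagree.

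**Conclusion.** The point holds as a contradiction with a possible bias. Sections 3.9.3.4.1 and 3.9.3.4.3 keep all patients seen from V2 and carry values forward for every drop-out, whereas section 3.9.3.4.4 makes inclusion or continued evaluation depend on the reason for leaving. On either reading of that section, costs and QALYs can be biased. The routes are selection on post-randomisation reasons, discretion in one listed case, and one ground that exists in a single arm.

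About 2 to 3 of 25 patients per arm would be affected. This assumes that drop-out is the planned 10% and occurs after V2. No bias in cost per QALY can be put in figures, because the mix of reasons, the utilities and the costs are not given; the direction could favour either arm. The point should be corrected before analysis. It concerns the economic evaluation and changes no sample size figure.

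**What to change.** Replace sections 3.9.3.4.1 and 3.9.3.4.4 with one rule for both arms:

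1. **Population.** Analyse patients in their allocated arm, preferably all randomised patients. Randomisation is at V1, so starting at V2 omits anyone lost in between. A V2 start would also remove the contradiction if applied alike to both arms, but it leaves that gap.
2. **Follow-up.** Delete the list of reasons as a condition for inclusion or follow-up. Continue EQ-5D and cost collection to the planned visits for every drop-out, whatever the reason, unless the patient withdraws consent to data collection. Section 3.2 already provides telephone and online routes.
3. **Missing data.** State one missing-data rule for the economic outcomes and apply it to both arms and to all reasons for drop-out.

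Reasons for drop-out can still be recorded and reported by arm. The cost is new wording for two short sections and a few extra questionnaires for about 5 patients (2 × 2.5) at the planned drop-out rate.
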